## Abstract

**Aims:**

To evaluate the effectiveness of a multicomponent exercise intervention and to clarify the underlying mechanisms of the program in community-dwelling older adults with cognitive frailty. Additionally, the perception of participants in the program will be explored.

**Design:**

A mixed-methods design, including a randomized controlled trial and an exploratory qualitative study, was used.

**Methods:**

Each group consists of 41 participants. The experimental group will undergo a 12-week multicomponent exercise intervention, including warm-up, exergaming aerobic exercise, elastic-band resistance exercise, and cool-down. This intervention was developed based on the Health Belief Model (HBM) and Self-Efficacy Model (SEM). The control group will not receive any intervention. Physical frailty and cognitive function will be considered as primary outcomes. Data will be collected both at baseline and at the end of the intervention period. Fisher’s exact test, analysis of covariance, and generalized linear models will be conducted to compare mean changes between the two groups. Additionally, the mediation models will be used to examine whether any intervention effects are mediated through exercise self-efficacy.

**Discussion:**

The findings of this study are anticipated to provide valuable insights for healthcare providers, enabling them to learn about effective strategies to enhance exercise adherence and promote improved functionality, independence, and quality of life for older adults with cognitive frailty.

Clinical trial registration: [https://clinicaltrials.gov/], identifier [ChiCTR2200058850].

## Introduction

1

Physical frailty emerges as a prevalent geriatric syndrome globally, which is characterized by age-associated declines in physiologic reserve and function across multiorgan systems (Fried et al., 2001). One of the most common physical frailty models described in the literature is the Fried frailty phenotype, which defines frailty as a clinical syndrome meeting three or more of the five indicators: unintentional weight loss, physical inactivity, exhaustion, weakness, and slowness (Fried et al., 2001). One recent systematic review provides prevalence proportions for older adults in population-level studies from 62 countries/territories for using the Fried frailty phenotype approaches to define frailty, generating a pooled prevalence of 12% for physical frailty (O’Caoimh et al., 2020). Physical frailty overlaps with other geriatric syndromes, such as cognitive impairment, resulting in increased vulnerability to various adverse health outcomes (Kelaiditi et al., 2013; Chu et al., 2021).

Cognitive frailty has been defined as the presence of both physical frailty and cognitive impairment without a clinical diagnosis of Alzheimer’s disease and other dementias (Kelaiditi et al., 2013). The prevalence of cognitive frailty among community-dwelling older adults is 6% (Zhang et al., 2022). Compared to either physical frailty alone or cognitive impairment alone, cognitive frailty poses a higher vulnerability to adverse outcomes, including disability, dementia, and mortality (Kelaiditi et al., 2013; Ruan et al., 2015). Cognitive frailty has been considered an intervention window because older adults with cognitive frailty are more likely to revert to a robust state through appropriate interventions compared to those with dementia and disability (Solfrizzi et al., 2017). Research has shown that exercise intervention is a highly recommended strategy for improving the health outcomes of older adults with cognitive frailty (Chen et al., 2021). Exercise, as a subset of physical activity, is characterized by planned, structured, and repetitive implementation (Caspersen et al., 1985; Thivel et al., 2018). It aims to improve or maintain one or more components of physical fitness (Dasso, 2019). Exercise can be performed in different forms and can differ in intensity, duration and type (e.g., aerobic and strength). According to the American College of Sports Medicine (ACSM) recommendations, multicomponent physical activity, including both aerobic and muscle-strengthening activities, should be adopted among older adults (Nelson et al., 2007).

## Background

2

Older adults with cognitive frailty are acknowledged to be frailer compared to their healthier peers. Furthermore, they tend to have sedentary lifestyle and engage less in physical activity (Kwan et al., 2020). Research has indicated that a sedentary lifestyle and physical inactivity are associated with adverse health outcomes (Theou et al., 2017). Conversely, physical exercise may enhance physical performance, cognitive function, and mental health in individuals with cognitive frailty (Yoon et al., 2018; Chen et al., 2021; Li et al., 2022). This highlights the importance of promoting physical exercise within this group.

However, it is challenging to change people’s physical exercise behaviors. Adherence to physical exercise interventions is often low among older population (Valenzuela et al., 2018; Moral-Munoz et al., 2022). Exercise adherence plays a crucial role in determining whether and how much the exercise intervention could be effective. Some exercise interventions have failed to achieve the intended effectiveness due to poor exercise adherence (Clegg et al., 2014; Gwyther et al., 2018). Previous studies have identified common reasons for this lack of adherence, such as physical limitations, environmental barriers, and time constraints (André and Agbangla, 2020; Collado-Mateo et al., 2021). Additionally, lack of motivation and enjoyment of exercise have been recognized as significant factors influencing adherence (André and Agbangla, 2020; Collado-Mateo et al., 2021).

Exergaming, a form of enjoyable aerobic exercise-based video games that combine physical activity and cognitive stimulation within a virtual environment, has emerged as an innovative way to encourage exercise among older adults (Choi et al., 2017; Karssemeijer et al., 2019). Several studies have examined the adherence and effectiveness of exergaming in older adults, revealing promising results that underscore its ability to enhance motivation for sustaining exercise programs (Lamoth et al., 2011; Altamimi and Skinner, 2012). However, while these programs target older people in general, they do not focus on older adults with cognitive frailty (Cacciata et al., 2019; Yen and Chiu, 2021). Additionally, these exergaming programs typically focus solely on aerobic activities, lacking of muscle-strengthening exercises, which may potentially limit their overall health benefits (Stojan and Voelcker-Rehage, 2019; Esmaeilzadeh et al., 2022). The ideal exercise prescription for older individuals should incorporate both aerobic and muscle-strengthening exercise (Venegas-Sanabria et al., 2022). Both forms of exercise are crucial for successful performance in activities of daily living (ADLs) and for maintaining physical and psychological wellbeing (Chodzko-Zajko et al., 2009). Relying solely on a single form of exercise may not provide comprehensive benefits (Chodzko-Zajko et al., 2009).

Furthermore, the selection of assessments is pivotal in intervention studies. Previous studies among cognitive frailty have predominantly focused on intervention effectiveness related to frailty, cognitive function, muscle-related outcomes, physical functional abilities, and quality of life. However, there’s been a lack of attention to intervention effects on senior fitness, sleep quality, and mental health (Yoon et al., 2018; Kwan et al., 2020). Researchers are encouraged to explore the effectiveness of exercise interventions from a broad perspective for comprehensive effectiveness evaluation, considering exercise interventions have been proven to offer a wide range of health benefits (Qiao et al., 2022).

Moreover, most previous exercise studies lack a theoretical basis for understanding exercise behavior change (Hauer et al., 2020; Huang, 2020), thereby limiting the exploration of potential intervention mechanisms among older adults with cognitive frailty. Currently, the Health Belief Model (HBM) and the Self-Efficacy Theory (SET) are two commonly used theoretical frameworks in physical exercise research (Biddle and Nigg, 2000). Our proposed intervention program is guided by theoretical constructs drawn from the HBM and SET (Figure 1). Self-efficacy, defined as one’s confidence in performing particular behaviors, significantly influences health behavior performance, subsequently impacting health outcomes (Bandura, 1994). Perceived threat, perceived benefits, perceived barriers, mastery experience, verbal persuasion, and physical and psychological states stand as key sources contributing to self-efficacy (Bandura, 1994). Studies have shown that self-efficacy predicts physical exercise behavior in older adults and plays a role in both the adoption and maintenance of physical exercise (Di Maio et al., 2021; Bateman et al., 2022). Additionally, experimental findings support the idea that changes in self-efficacy can act as a mediator in the impact of behavior interventions on objectively measured physical exercise behavior (Ratz et al., 2020).

**Figure 1 fig1:**
[figure not shown]
Conceptual framework for the intervention.

The proposed intervention aims to enhance the participant’s self-efficacy by employing a series of model-based behavior health technique. Techniques such as reminders, goal setting, encouragement, and feedback, when coupled with incentives, serve as motivators to improve self-efficacy (Ashford et al., 2010; Eather et al., 2013; Lewis et al., 2016). Consequently, the intervention program, incorporating multicomponent exercise training and model-based behavior health technique, is hypothesized to provide older adults with a stronger sense of self-efficacy, leading to increased physical exercise and improved health outcomes.

Therefore, the objectives of this study were: (1) to evaluate the effectiveness of a multicomponent exercise intervention in improving the health outcomes (physical frailty, cognitive function, body composition, senior fitness, mental health, sleep quality, and health-related quality of life) among older adults with cognitive frailty; (2) to examine whether any health-improving effects are mediated through exercise self-efficacy; and (3) to explore the participants’ perception of the multicomponent exercise intervention.

## Methods

3

### Research hypotheses

3.1

To assess the impact of the multicomponent exercise intervention, our study hypothesizes several outcomes across physical, cognitive, mental, and quality-of-life domains. We aim to explore the potential effects of this intervention on various parameters and examine the mediating role of exercise self-efficacy.

(1) We hypothesized that participants who receive the multicomponent exercise intervention will report greater improvements in physical frailty, cognitive function, body composition, senior fitness, mental health, sleep quality, and health-related quality of life upon completion of the intervention compared to those in the control group.(2) We hypothesized that the effects of the multicomponent exercise intervention on physical frailty, cognitive function, body composition, senior fitness, mental health, sleep quality, and health-related quality of life are mediated through an increase in exercise self-efficacy.(3) No starting hypothesis has been established for the qualitative part of the study because it is oriented through an exploratory study.

### Methodology

3.2

#### Study design, setting, and participants

3.2.1

This mixed methods study comprises a single-blind (outcomes assessor) randomized controlled trial (RCT) and a descriptive qualitative study. It will be conducted in community settings targeting older adults with cognitive frailty in Changsha City, Hunan Provence, China. Community settings will be chosen based on approval from local committees and the availability of eligible older adults. To engage older residents and encourage their participation, we will utilize posters, flyers, and social media platforms to disseminate information about the study. Additionally, recruitment will be conducted in collaboration with healthcare personnel who are responsible for the preventive home visits for the local residents.

Inclusion criteria:

(1) Aged ≥60 years.(2) Fulfilling the definition of cognitive frailty, which includes:(a) pre-physical frailty or physical frailty (Fried frailty phenotype score ≥ 1), and.(b) Montreal Cognitive Assessment (MoCA) scored between 18 and 25, but in the absence of dementia (Kelaiditi et al., 2013).(3) Providing informed consent and voluntary participation in the study.

Exclusion criteria:

(1) Poorly controlled or severe status of cardiovascular diseases, chronic obstructive pulmonary disease, diabetes, or hypertension.(2) Inability to walk independently.(3) Severe hearing or visual impairments.(4) Other health conditions that prevent participation in sports exercise.(5) Currently enrollment in other intervention programs.

The trial will run for a 12-week period. Participants will be enrolled based on inclusion and exclusion criteria. Measurements will be conducted at baseline and at the end of the intervention period. An overview of the study design is presented in Figure 2. Regarding the qualitative study, a subgroup of participants assigned to receive the multicomponent exercise intervention will undergo semi-structured interviews to explore their perception of the program.

**Figure 2 fig2:**
[figure not shown]
Study design.

#### Intervention

3.2.2

Based on literature review, interviews with cognitive frail older adults, and consultations with physiotherapist, a preliminary multicomponent exercise intervention has been recommended for older adults with cognitive frailty. During the 12-week multicomponent exercise intervention period, participants will engage in moderate physical exercise tailored to their individual abilities, with each session lasting 50 min, held 3 times per week in a group setting at the local community center. Trained research assistants will provide assistance during these sessions. To control for concomitant exercise and diet, all participants will be advised not to seek any other exercise and instructed to maintain their normal diets throughout their enrollment in the study.

The daily session will be divided into warm-up, exergaming aerobic exercise, elastic-band resistance exercise, and cool-down. Each session will start and end with a 5-min warm-up and cool-down routine to stretch the main muscle groups being trained. Ping-Pong exergaming on the Xbox 360 4GB Console with Kinect will be chosen as the aerobic exercise because Ping-Pong is familiar to most older adults in China and requires fewer skills compared to other types of exergaming. This type of exergaming is suitable for older adults with cognitive frailty because it is easier to learn. The progression of ping-pong exergaming will be managed by adjusting the exercise intensity. The duration of the ping-pong exergaming would be approximately 20 min per daily session. The intensity will be gradually increased throughout the entire intervention period based on the self-reported tiredness and assessment conducted by trained exercise supervisors. Resistance exercise will utilize an elastic band (Thera-Band elastic band). The general recommendation will be an exercise intensity of 70–80% of 1 repetition maximum (1RM) allowing older adults to perform 8–10 repetitions (Liguori and American College of Sports Medicine, 2020). The duration of the resistance exercise will be about 20 min per session. The elastic-band is color-coded, with different colors representing different levels of resistance. In this study, yellow, red, green, and blue elastic-bands will be used alternately to increase resistance intensity. To ensure participants exercise at the appropriate intensity, their perceived effort levels will occasionally be assessed using the Borg Rating of Perceived Exertion scale, which ranges from 6 to 20 (Borg, 1982). Participants will be asked to report their average intensity level during the exercise sessions. Depending on the participant’s fitness level, exercises should be performed with a perceived exertion range between 9 and 16 points during both aerobic and resistance training (Borg, 1982). Further details are presented in Table 1. The final exercise intervention protocol will be determined based on a pilot study involving 10 participants to assess feasibility.

**Table 1 tab1:** Description of the multicomponent exercise intervention.

Category	Description
Warm-up	Freehand training range of motion exercise for the wrists, hip, shoulder, knees, and ankles (about 5 min)
Aerobic exercise	Exergaming-based Ping-Pong aerobic exercise involves dynamic body movements, including swinging motions with virtual Ping-Pong paddles, upper body rotation to hit the ball accurately, and leg movements to position oneself correctly (about 20 min)
Resistance exercise	The action includes elastic-band pull-apart, front and lateral raises, elbow flexion/bicep curl, and elastic-band lateral leg abductions, etc. (about 20 min)
Cool-down	Freehand stretching and relaxing exercises involve the main muscles and joints of the whole body (about 5 min)

In the control group, participants will maintain their normal daily activities without receiving any special intervention. Throughout the 12-week intervention period, if participants engage in additional physical activity, they will be required to document the details, including the activity time, type, and intensity. To avoid cross-contamination between the two groups, control over the exergaming power switch will remain with the intervention team, not the participants. Additionally, the elastic bands provided during sessions will be collected afterwards rather than kept by the participants.

#### Strategies to support behavior change

3.2.3

To enhance adherence to the multicomponent exercise intervention, strategies supporting behavior change will be implemented, integrating elements from the HBM and SET. Previous studies suggest that exercise interventions among older adults should prioritize strengthening their beliefs and self-efficacy. This involves educating them about the negative consequences of physical inactivity, highlighting the benefits of exercise, and teaching coping strategies to overcome potential barriers. It also focuses on helping participants mastery exercise experiences, maintain good physical and psychological states, and employ persuasion strategies (Biddle and Nigg, 2000; McAuley and Blissmer, 2000; Glanz et al., 2015). Details of the behavior change techniques (BCTs) (Michie et al., 2011) and how they are incorporated into this exercise intervention program are presented in Table 2.

**Table 2 tab2:** Behavior change techniques used in this exercise intervention program.

Beliefs and self-efficacy	Behavior change technique	How the technique is in this intervention
Perceived threat (HBM)	Provide information on consequences of behavior in general	Health education, interveners give information about correlation between insufficient physical activity and potential adverse effects in the general case. Interveners reinforce the health risk of physical inactivity through WeChat group.
	Provide information on consequences of behavior to the individual	Interveners interpret the baseline assessment results for participants, describe to the participants the underlying impairments identified at the baseline assessment. Interveners reinforce the health risk of physical inactivity during the consultation.
Perceived benefits (HBM)	Provide information on consequences of behavior in general	Health education, interveners disseminate knowledge regarding the health benefits of physical activity. Interveners reinforce the health benefits of physical activity through WeChat group.
	Provide information on consequences of behavior to the individual	Interveners interpret the baseline assessment results for participants, describe to the participants the health benefits of physical activity.
Perceived barriers (HBM)	Barrier identification /problem solving	Interveners ask the participants possible barriers and problems, discuss and offer possible solutions in the Wechat group and during the consultation. A brief medical safety check before each session to reduce injury risk.
Mastery experiences (SET)	Provide instruction on how to perform the behavior	Provide instruction and support on how to use exergaming equipment and elastic-band. Tips on wearing suitable clothing, shoes, and avoiding empty stomach, reminding when and where of each session will be sent to WeChat group.
	Model/Demonstrate the behavior	Each session will have a model showing the participants how to perform the multicomponent exercise training.
	Facilitate social comparison	Interveners will encourage participants to communicate and compare with other participants during training.
	Action planning	At week 1, interveners tell participants of detailed planning of what they will do including when, where, and how to act.
Physical and psychological states (SET)	Goal setting	At week 1, interveners and participants set individual goals concerning exercise training based on consider of participants’ physical and psychological states.
	Stimulate anticipation of future rewards	Participants are informed at the beginning (week 1) that they will be rewarded based on their behavioral achievement.
Verbal persuasion (SET)	Provide information on consequences of behavior in general	Health education, interveners give information about correlation between insufficient physical activity and potential adverse effects in the general case. Interveners reinforce the health risk of physical inactivity through WeChat group.
	Provide feedback on performance	Participants will receive real-time feedback when playing exergaming. Intervener praise participants if they behave well during the training.
	Provide instruction on how to perform the behavior	Provide instruction and support on how to use exergaming equipment and elastic-band. Tips on wearing suitable clothing, shoes, and avoiding empty stomach, reminding when and where of each session will be sent to WeChat group.
	Provide normative information about others’ behavior	Intervener provide information about other’s good performance and encourage individuals to learn from successful experience through WeChat group.
	Prompt review of outcome goals	Intervener helps participants to review or analysis of the extent to which previously set outcome goals were achieved during the consultation.

#### Sample size estimation

3.2.4

For the RCT, the sample size will be calculated using PASS software, based on improvement in the primary outcome (physical frailty) in this trial. Previous findings from a similar exercise program reported a reduction in physical frailty score of 0.22 in the control group and 1.59 in the intervention group (Sadjapong et al., 2020). Given a power of 90% and level *α* = 0.05, 34 participants are needed. Considering a 20% attrition rate, with 41 participants in each group, a total of 82 participants are needed. Regarding the qualitative interviews, a purposive subsample of 20 participants who have completed the multicomponent exercise intervention will be recruited.

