#### Data analysis

3.2.10

Summary statistics, including means with standard deviations, frequencies, and percentages, will be generated for baseline characteristics. To compare the baseline characteristics between the two groups, Student’s *t*-test or the Wilcoxon rank-sum test will be utilized for continuous variables, while Chi-square or Fisher’s exact tests will be employed for categorical variables. Analysis of covariance (ANCOVA) and generalized linear models (GLM) will be performed to compare mean changes in continuous variables between the two groups. Adherence, dropout rates, program satisfaction, and adverse events will be tabulated and summarized using descriptive statistics. Mediation models will be used to test whether exercise self-efficacy mediates the relationship between the multicomponent exercise intervention and physical frailty, cognitive function, body composition, senior fitness, mental health, sleep quality, and health-related quality of life. Any missing data on outcomes will be approximated through multiple imputation. All analyses will be performed with the intention-to treat (ITT) principle. Two-sided tests will be performed for all analyses, and *p*-value less than 0.05 will be considered to be statistical significance. Additionally, sensitivity analyses will be adopted to assess the robustness of the findings based on the per-protocol analysis set.

Regarding qualitative data, audio-recorded interview will be transcribed word-for-word. Content analysis will be adopted to code the data on their perceptions of the intervention. Two authors will independently code the data, and any discrepancies will be resolved through discussion.

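### Minor arithmetic error: the 20% attrition allowance was applied as 34 × 1.2, so 41 per group covers about 17% attrition, not 20%

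*Protocol article*

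**What the plan says.** Section 3.2.4 of the protocol article bases the calculation on physical frailty. It takes from an earlier exercise study a "reduction in physical frailty score of 0.22 in the control group and 1.59 in the intervention group". It continues: "Given a power of 90% and level *α* = 0.05, 34 participants are needed". The attrition step follows at once: "Considering a 20% attrition rate, with 41 participants in each group, a total of 82 participants are needed". The formula for that step is not written out. The abstract repeats the result: "Each group consists of 41 participants". The data analysis section (3.2.10) adds "Two-sided tests will be performed for all analyses", and plans ANCOVA and generalized linear models under intention to treat, with multiple imputation of missing outcomes.

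**The concern.** An attrition rate is the share of enrolled participants who are lost. The number to enrol is therefore the number needed divided by the share retained. Raising the number needed by the attrition percentage is a common slip, and it always enrols too few. Section 3.2.4 prints all three quantities (34 needed, 20% lost, 41 enrolled per group), and they do not fit together. If 20% are lost, fewer than 34 per group remain; if 34 remain, attrition was below 20%. At stake is the accuracy of a headline design statement, 90% power after allowing for 20% loss, which the results paper would normally repeat.

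**Working it through.** **Inputs from section 3.2.4:** 34 needed, 20% attrition, 41 per group, 82 in total, 90% power, α = 0.05, mean reductions 0.22 and 1.59. Two-sided testing comes from section 3.2.10. The SD is not in the article and is treated below as an assumption.

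**Which reading of 34.** The article does not label 34 as per group or total. If it were the total (17 per group), inflation would give 17 × 1.2 = 20.4 or 17/0.8 = 21.25 per group, nowhere near 41. Only the per-group reading leads to 41 and 82.

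**Reproducing the stated figure.** 34 × (1 + 0.20) = 40.8, rounded up to 41 per group; 2 × 41 = 82. This matches exactly.

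**The size that 20% attrition requires.** 34/(1 − 0.20) = 42.5, rounded up to 43 per group; 2 × 43 = 86. The gap is 2 per group and 4 in total.

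**What each size leaves.**
- 41 per group with 20% lost: 41 × 0.80 = 32.8, short of 34 by 1.2.
- 43 per group with 20% lost: 43 × 0.80 = 34.4, enough.
- Largest attrition that 41 can absorb: 1 − 34/41 = 0.171, or 17.1%.

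**Effect on power.** The difference in mean change is 1.59 − 0.22 = 1.37. Assume an unadjusted two-sample t-test on change, two-sided 0.05, with power from the noncentral t distribution. Solving for the SD:
- 34 per group gives exactly 90% at SD = 1.717 (standardised difference 1.37/1.717 = 0.798).
- 33 per group gives exactly 90% at SD = 1.691 (standardised difference 1.37/1.691 = 0.810).

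SDs between these two values, about 1.69 to 1.72, are the ones that round up to 34 per group. Power over that range:

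| Evaluable per group | SD 1.691 | SD 1.717 |
|---|---|---|
| 34 | 90.9% | 90.0% |
| 33 | 90.0% | 89.1% |
| 32.8 (expected) | 89.8% | 88.9% |
| 32 | 89.1% | 88.1% |

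At the expected 32.8 completers, power falls short of 90% by 0.2 to 1.1 points. A loss of about 2 points needs both the largest SD and a chance outcome of only 32 completers.

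**The case against.** Four points can be made for the plan.

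*The effect is trivial.* The expected shortfall is about one completer per group and at most about one point of power. This stands, and it sets the weight of the point: it does not touch the design, the conduct or the interpretation of the trial.

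*The planned analysis may recover the loss.* ANCOVA adjusted for baseline can be more precise than a t-test on change. With equal variances at both visits and baseline to follow-up correlation r, the variance is multiplied by (1 + r)/2. With 32 per group and SD 1.717, power is then about 97% at r = 0.3, 95% at r = 0.5, 93% at r = 0.7 and 89.7% at r = 0.9. The article gives no r, so this is a range and not a demonstration. It does mean that actual power may well exceed 90%. It does not repair the attrition step, because 34, 20% and 41 still disagree.

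*Multiple imputation keeps everyone in the analysis.* Imputation does not in general restore all the information lost with a missing outcome. The article's own calculation treats dropouts as lost, which is why it inflates 34 at all.

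*The article is condensed.* A reader might infer that the missing SD and the missing per-group label are further errors, or that 34 cannot be justified. The documents do not support that. A journal article may leave such details to the full protocol, the source study may supply the SD, and the next sentence settles the per-group reading. The point here is not an omission: the three printed figures conflict.

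**Conclusion.** The point holds as a minor arithmetic error. The planned 41 per group corresponds to about 17% attrition, not the stated 20%; at 20% about 32.8 per group would be evaluable against the 34 that the article says are needed. This part rests only on the article's own figures, with 34 read as per group. The power cost, roughly 88.9% to 89.8% instead of 90%, rests on two assumptions that the article does not state: an unadjusted two-sided t-test, and an SD of the change of about 1.69 to 1.72. A reader might go further and conclude that the trial is underpowered or must recruit more participants. The documents do not support that: the gap is about a point at most under the t-test, and baseline adjustment could more than close it.

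**What to change.** Correct the attrition sentence in section 3.2.4 in one of these ways:

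1. Keep 41 per group (82 in total) and state the allowance as about 17%.
2. Keep 41 per group and 20% attrition, and state that about 33 per group are expected to be evaluable, with power of about 89% to 90%. The exact figure should come from the SD and test used in the original PASS run.
3. If 90% power and 20% attrition are both to be kept, set the size at 43 per group (86 in total) and change the abstract to match.

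The first two are changes of wording only; the price is a stated allowance 3 points lower, or stated power up to about one point lower. The third adds 4 participants. While the sentence is open, labelling 34 as per group would help the reader, but the correction does not depend on it.
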